## 2.2 Complementary Medicine for Vascular Dementia

In the absence of satisfactory pharmacological therapy, many patients and their carers turn to complementary medicine. The use of herbal medicine for the treatment of ageing-related disorders was documented in the literature more than 2000 years ago in ancient China where herbal remedies were used to boost memory function and increase longevity. A literature review conducted by our team has revealed a large number of preclinical and clinical studies indicative of the potential benefits of herbal medicines in VaD and/or dementia. Specific herbs of particular promise include *Ginkgo biloba*, *Panax ginseng*, *Bacopamonniera*, Huperzine A (an alkaloid extract isolated from a moss, *Huperziaserrata*), *Crocus sativus* and vinpocetin

(vinca alkaloid derived from the leaves of *Vinca minor*). In reviewing these herbs and their actions, we have identified three of particular interest (*Ginkgo biloba*, *Panax ginseng*, *Crocus sativus*), which led to our series of preliminary studies described below.

*Ginkgo biloba*: *Ginkgo biloba* leaf extract (ginkgo) has been widely used for management of ageing-related memory disorders. The principal constituents of ginkgo are flavonol glycosides (e.g., quercetin and kaempferol) and terpenoids (e.g. ginkgolide and bilobalide). Data from preclinical studies suggest that ginkgo decreases oxygen radical discharge and proinflammatory functions of macrophages (antioxidant and anti-inflammatory), reduces corticosteroid production (anxiety), increases glucose uptake and utilization and ATP production. In addition, ginkgo appears to improve blood flow by increasing red blood cell deformability, decreasing red cell aggregation, inducing nitric oxide production and antagonising platelet activating factor receptor.

In healthy young adults, ginkgo treatment has been shown to improve speed of processing, working memory, executive function and cognitive function. A recent systematic review revealed that memory enhancement is the most robust acute effect of ginkgo in young adults. In clinical trials with dementia patients (including VaD) however, the effectiveness of ginkgo for enhancing memory and cognitive function remains controversial. Numerous controlled clinical trials demonstrated various levels of improvement in memory loss, concentration, anxiety and other symptoms associated with dementia. For example, a randomized, double-blind, placebo-controlled trial of 216 participants with AD or VaD showed significant improvements in the attention and memory function in the EGb761 (a standard ginkgo preparation) treated group after 24 weeks treatment. Two more recent studies also demonstrated therapeutic benefits of ginkgo, especially in patients with neuropsychiatric features of dementia. In contrast, several clinical trials with greater numbers and longer interventions reported no difference between ginkgo and placebo interventions in dementia treatments, which led to the conclusion in a recent Cochrane systematic review that the existing evidence to support the use of ginkgo remains inconsistent and unconvincing. However, a newly published meta-analysis, that considered the baseline risk in the assessment of treatment effect, has shown 6 months of treatment with ginkgo is associated with a significant improvement of cognitive function in dementia patients.

It is worth noting that almost all existing clinical trials used the standardised ginkgo preparation, EGb 761. Assessment of other ginkgo preparations that may have different chemical profiles of

active constituents, and preparations where ginkgo is used as part of a formulation (possibly having synergistic effects with other components – see below) is lacking.

*Panax ginseng* (ginseng) is widely used to treat VaD and other dementias. The principal bioactive components of ginseng are ginsenosides, which have been suggested to have antioxidant, anti-inflammatory and anti-apoptotic effects. Several studies have reported that ginseng modestly improved thinking and learning capacity. A 12 month randomized controlled trial evaluating a ginseng extract for the treatment of VaD in China, found that ginseng significantly improved memory function. Studies conducted by Stough and Scholey found that ginseng also produces an EEG profile similar to ginkgo, which is consistent with its role as a cognition enhancer. In a series of acute and chronic studies of in humans, the ginseng established robust enhancement of secondary and working memory, which may be related to the ability of ginseng to normalise blood glucose levels.

*Crocus sativus* (saffron) is commonly used in traditional Chinese medicine as an antidepressant, antispasmodic, and anticatarrhal. Data from *in vivo* and *in vitro* studies demonstrated that saffron possesses neuroprotective properties. Saffron extract has shown to improve learning and memory function in ethanol-induced memory impairment in mice and to ameliorate cerebral ischemia induced oxidative damage in rat hippocampus. Crocetin, the principal constituent of saffron and a strong antioxidant, is suggested to be largely responsible for saffron's protective effect on the central nervous system.

Multisystem approach of Chinese herbal medicine: Combination therapy underpins the philosophy of Chinese herbal medicine, where patients are generally treated with multi-herbal formulations. There is preliminary evidence that complex chemical mixtures enhance therapeutic efficacy by facilitating synergistic action and/or ameliorating/preventing potential side effects. Synergistic effects can occur in many ways, including for example, where constituents from herbal extracts interact with one another to improve their solubility and hence the bioavailability. Furthermore, constituents of complex herbal extracts can affect different targets, which make them ideal therapies for disorders such as VaD, which have multifactorial/multisystem pathophysiological components. Clinical studies in healthy volunteers demonstrate the cognitive effects of a ginkgo-ginseng combination far outweigh those of either extract alone, suggesting the possibilities of synergistic interactions between the extracts. Of particular relevance to this study is that this effect was most marked on those tasks which are known to rely on effective cerebral blood supply.

## 2.3 Sailuotong (*SLT*), a standardised Herbal Formulation for VaD

Formulation background: The research team at Xiyuan Hospital has utilised the multi-system approach of Chinese herbal medicine to develop a three-herb formula (*SLT*) combining specific dosages of *Panax ginseng* C A Mey (ginseng), *Ginkgo biloba* L (ginkgo), and *Crocus sativus* L (saffron) for the management of VaD. *SLT* represents a new generation of herbal formulation where the chemical and pharmacological profiles have been clearly defined using modern chemistry, pharmacognosy and pharmacology techniques. To determine the optimal ratio of the three herb extracts in *SLT*, eight different combinations of ginkgo, ginseng and saffron extracts have been studied using orthogonal pharmacokinetic design in the right middle cerebral artery ligation induced ischemia model in rats and Morris water maze model in mice to evaluate their efficacy in improving the ischemic area of the brain and memory function. The data demonstrated that the herbal extracts in descending order of significance were ginseng, ginkgo and saffron. The optimal ratio of the three herbal extracts was 5:5:1 and the optimal dosage of *SLT* extract was 22 mg/kg in mice. This figure was converted to a human dose equivalent through a surface area dosage conversion and the consideration of the approved human doses provided in the Pharmacopeia of the People's Republic of China.

Pharmacological studies of *SLT*: A series of preclinical pharmacokinetic and pharmacodynamic studies were conducted on the three individual herbs and in combination. The data from these experiments demonstrate significant improvements in learning and memory functions, pathogenic biochemical parameters in blood and brain tissue, and antioxidant capacity in various experimental dementia models.

In an *in vivo* study, *SLT* (11, 22, and 44 mg/kg per day over 15 days) was administered to dysmnnesia models in mice induced by scopolamine, reserpine, chlorderazin, sodium nitrite, and alcohol, respectively. Compared with the control, the middle and high dose treatment of *SLT* markedly decreased the error numbers and prolonged the latencies of dysmnnesia in all active groups. In a chronic cerebral hypoperfusion model induced by bilateral common carotid artery ligation in rats, 8 weeks treatment of *SLT* (ig) significantly shortened the persistent time for finding the platform in Morris Water Maze. Activity of cholinesterase was also significantly decreased ( $p<0.05$ ) while the ACh level was markedly increased in the brain tissue ( $p<0.05$ ). In addition, the activity of superoxide dismutase (SOD) was significantly enhanced ( $p<0.05$ ). The effects of *SLT* on ACh were also investigated in an amyloid  $\beta$ -protein induced dementia model in mice. After 30 days treatment of *SLT* (15.5 and 31.0 mg/kg per day, ig), ACh levels in the

brain tissue increased by 18.56% and 19.97%, respectively, when compared with the model group (Figure 1). Both changes reached statistical significance ( $P < 0.05$ ). Similarly, in a PDAPPv7171 transgenic dementia model in mice, *SLT* treatment at 31 and 62 mg/kg per day i.g. over 12 weeks significantly increased ACh in both treatment groups, while serotonin (5-HT) levels in the brain tissue decreased significantly in the high dose *SLT* group only. The effects of crocin alone (the principal active component of *Crocus sativus*) on ischemia/reperfusion (I/R) injury were investigated using a global or bilateral common carotid artery occlusion (BCCAO) model in mice. Transient global cerebral ischemia (20 min), followed by 24 h reperfusion, significantly increased the production of nitric oxide (NO) and malondialdehyde (MDA) in cortical microvascular homogenates and decreased the activities of superoxide dismutase (SOD) and glutathione peroxide (GSH-px). Pre-treatment with crocin at 20 mg/kg, on the other hand, resulted in a significant decrease in MDA content (Figure 2) and a significant elevation in total antioxidant capacity (increased SOD ( $p = 0.000$ ) and GSH-px ( $p = 0.001$ ) activities).

**Figure 1 Effect of Sailuotong (SLT) on ACh in A $\beta$ -treated rats (n=12, Mean $\pm$ SD). bP<0.05 vs control group; eP<0.05 vs model group**

[figure not shown]

**Figure 2 Effect of crocin on MDA levels in cerebral microvascular homogenates after 20 min of BCCAO with 24 h reperfusion (n=10, Mean  $\pm$  SD). \*\*\*p<0.001 compared with I/R group; ### p< 0.001 compared with I/R group with crocin treatment (5 mg/kg)**

[figure not shown]

Animals studies in anesthetised dogs have also demonstrated that *SLT* treatment (8.25, 16.5 and 33 mg/kg over 24 h) significantly decreased the areas of focal cerebral ischemia/reperfusion injury in mice. A significant increase in cerebral blood flow was observed after administration of *SLT* (10 mg/kg for 60 - 180 min). *SLT* treatment (16 mg/kg and 8 mg/kg for 7 days) also significantly decreased the platelet aggregation rate and whole blood viscosity in rats.

**Safety of *SLT*:** Acute toxicity tests on *SLT* were undertaken in mice. The maximum tolerated dose (MTD) for the formula as whole, ginsenosides, flavone-glycosides and crocins was 1.7g/kg, 4 g/kg, 1.3 g/kg, and 5.0 g/kg, respectively, all of which were significantly higher than the proposed clinical dose (655x, 3422x, 1109x and 21386x respectively). A long term toxicity study was also conducted in dogs. The MTD of *SLT* is 200 mg/kg, which is 70 times higher than the clinical dose. In an *in vitro* study, the inhibitory capacity of *SLT* was evaluated on five cytochrome P450 isoenzymes recommended by the US FDA for drug interactions studies. The median inhibitory concentration (IC50) values for CYP1A2, CYP2B6, CYP2D6,

CYP2E1 and CYP3A4 were 50-140 fold higher than those potentially achievable by the therapeutic dose. This indicates that *SLT* treatment is unlikely to cause significant herb-drug interactions.

Phase I studies: Two Phase I clinical studies were conducted including a single dose study and a multiple dose study. In the single dose study, 30 healthy volunteers were allocated to 7 *SLT* dosage groups receiving 60 mg, 120 mg, 180 mg, 240mg, 300 mg, 420 mg, or 540 mg of *SLT*, respectively. Each participant only received one dose starting from the smallest allocated dosage. A larger dosage would only be given when no adverse effect was reported in the previous dosage group. In the multiple dose study, 24 healthy participants were randomly allocated to the treatment and placebo control groups, each containing 12 participants receiving 180 mg or 300 mg of *SLT* Capsules and 3 or 5 placebo capsules over 14 days, respectively. The following adverse events were observed in the studies including stomach discomfort, urticaria, local skin pain, diarrhoea, itchy skin, dry mouth, heartburn, abdominal distension, dizziness, and nausea, among which dizziness, nausea, dry mouth, and abdominal distension were "unable to be determined" to relate to *SLT*. There is no significant difference in the proportion of these adverse events between the treatment group and placebo group in the multiple dose study. The distribution of adverse events was not dose-related. No abnormal *SLT*-related changes in liver & kidney functions and ECG were observed. In the single dose study, 86.7% (26/30) of the trial participants experienced various degrees of decline of the fibrinogen level but no dose-effect relationship was observed. In the multiple dose study however, no downward trends in fibrinogen level were found with the prolonged treatment of *SLT*. There was no significant difference in fibrinogen levels between the *SLT* and placebo groups and therefore the observed changes of fibrinogen in the single administration study may not relate to the trial medication.

Pilot trial of *SLT*: A pilot randomized, double-blind, placebo-controlled clinical trial of *SLT* was recently completed in Sydney with promising results. Sixty-two patients (32 in the active group, 30 in the placebo group) with probable or possible VaD, were recruited according to the National Institute for Neurologic Disease and Stroke and the Association Internationale pour la Recherche et l'Enseignement en Neurosciences (NINDS-AIREN) criteria. Patients received 16 weeks of treatment with either active compound or identical placebo after randomization. At completion of treatment, the mean scores of the primary efficacy parameter, ADAS-cog reduced from 24.48 to 20.30 (mean reduction,  $4.18 \pm 0.75$ ) in patients receiving *SLT* and from 18.98 to 17.81 (mean reduction,  $1.18 \pm 0.58$ ) in patients receiving the placebo. Although the baseline characteristics of ADAS-cog differed slightly (statistically insignificant) between the two

groups, ANCOVA analysis with the ADAS-cog baseline scores as a covariate showed that the improvement of ADAS-cog scores was significantly greater in the *SLT* group than those in the placebo group ( $p < 0.005$ ). These results are consistent with the findings from a Single Photon Emission Computed Tomography (SPECT) study of the brain, with a sub-group of patients ( $n = 7$  *SLT*;  $n = 11$  placebo). The SPECT scan results showed that when compared to the placebo, the *SLT* treatment appeared to increase blood flow in the inferior frontal and anterior temporal lobes, and was more marked on the left. These regions are known to be associated with cognitive, memory, auditory and speech functions of the brain. *SLT* also significantly reduced the degree of impairment in quality of life caused by VaD as evident by the significant improvement in SF36 scores. Out of 8 domains, significant improvements were observed in the domains of ‘role emotion’, ‘mental health’, ‘role physical’ and ‘social functioning’ in patients receiving *SLT*, while significant trends towards improvement were also noted in two other domains - ‘physical functioning’ and ‘bodily pain’. No significant differences were found in the placebo group. Two patients out of 64 recruited developed moderate insomnia and headache respectively within the first two weeks of the treatment. Both patients withdrew from the study and were later found to be in the *SLT* treatment group. In both patients, their symptoms subsided on discontinuation of the treatment. No serious adverse events were observed in this pilot trial.

### 3. METHOD

#### 3.1 Study Design

This study will be conducted as a two-arm randomized, double-blind, placebo controlled clinical trial of 65 weeks, including a 52 week intervention and 13 week follow-up.

For a two-arm trial, participants will be randomized after informed consent is obtained, into two parallel treatment groups:

- a. Intervention group taking *SLT* (Active)
- b. Placebo control group (Placebo)

The trial will be double-blinded, such that the participants and investigators (including persons responsible for data collection, data management and data analysis) will not be aware of randomization assignments. No pilot study and no run-in period are required for this trial.

#### 3.2 Sample

##### Sample Size

Following the release of the Phase II SLT trial results, sample size for this study was recalculated as the two studies used very similar participant cohorts and study design. In particular, the Phase II study provided useful data for VADAS-cog, one of the primary outcomes for the current study. Sample size was calculated using the Phase II trial outcome data for the two primary measures (VADAS-Cog and ADCS-ADLs). Based on their VADAS-Cog data, we expect the minimum between-group endpoint to be 3 or more units (with a standard deviation of 6.56) for a clinically meaningful change in cognition. Using a one-sided independent samples t-test for the purpose of calculating sample size, a total of 166 participants are required to detect this difference with 90% power at the 0.05 significance level. For the ADCS-ADLs, we anticipate the minimum between-group endpoint to be 3 or more units (with a standard deviation of 5.31) for a clinically meaningful change in daily functioning. Using a one-sided independent samples t-test for the purpose of calculating sample size with this measure, a total of 110 participants are required to detect this difference with 90% power at the 0.05 significance level. Allowing for a total non-compliance/withdrawal rate of 30%, 238 participants will be recruited into the trial across all centres to ensure 166 participants in the final analyses.

For the MRI scanning sub study, to calculate the number of participants required repeated measures analysis of variance was used to examine the power of this study comprising 50 samples with two matched groups measured at two time points. Between factor repeated measures analysis was used to compute the power using the software G\*power. Assuming a medium effect size of 0.25, between-measures correlation of 0.5 at 5% level of significance the power was found to be 52%. However accounting for multiple hypotheses tests within the project the power may be reduced significantly. All participants who agree to participate in the main study will be asked if they would like to undergo MRI scanning until 50 participants are recruited. Although it is not possible to ensure equal numbers of treated and placebo participants undergo MRI scanning, that participants will be recruited into the main study in blocks of 6, each of which contain an equal number of treatment and placebo groups, it is likely that the number of treated and placebo participants in the MRI group will be similar.

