### **Missing data and protocol violations**

In the case of death, all measurements prior to death will be included in the analysis but all after death will be set to missing. To address withdrawals, loss to follow-up or non-compliance with the study analyses will be conducted on both an intention to treat (ITT) and per protocol (PP) basis. Withdrawing and non-compliant participants shall be encouraged to continue with data collection even if stopping treatment. Where data items are missing the last value carried forward method to replace missing data in the ITT analysis will be used. Participants who have significant deviations from the protocol will be removed from the PP analysis after the completion of the ITT analysis. Such significant deviations from the protocol will be determined and documented by the study clinician during the course of the study. Any deviation from randomisation, missing data and withdrawals will be fully reported for this purpose.

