### **Primary efficacy analysis**

The primary analysis will be linear mixed models through which we will test for differences between treatment groups on each outcome over time, with adjustment for random variation between treatment centres, with and without adjustment for other potentially important predicts (e.g. compliance, age, gender, severity of VaD). Non-linear changes over time will be tested by a) fitting time as categorical variable and b) testing for quadratic and cubic effects. Results will be reported as regression coefficients (or odds ratios if categorical) and associated 95% confidence intervals.

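### The 90% power in section 3.2 holds for a one-sided 5% test; on the two-sided standard implied by the 95% confidence intervals, 166 analysed give about 83% for VaDAS-cog, and the intention-to-treat power is left open

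*Protocol*

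**What the plan says.** Protocol section 3.2 (Sample Size) sizes the trial separately on its two primary scales. For each, the planning difference is 3 units, with a standard deviation of 6.56 for VaDAS-cog and 5.31 for ADCS-ADL. The method, a one-sided t-test, is stated openly, and for VaDAS-cog the result is that "a total of 166 participants are required to detect this difference with 90% power at the 0.05 significance level". The same one-sided method gives 110 in total for ADCS-ADL. Both figures are quoted at 90% power and a 0.05 level. The larger is then inflated: "Allowing for a total non-compliance/withdrawal rate of 30%, 238 participants will be recruited into the trial across all centres", so that 166 remain for the final analyses.

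Section 5.2 (Primary efficacy analysis) plans linear mixed models that test for treatment differences on each outcome over time. "Results will be reported as regression coefficients (or odds ratios if categorical) and associated 95% confidence intervals". It does not say whether the tests are one-sided or two-sided.

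Section 5.2 (Missing data and protocol violations) says that "analyses will be conducted on both an intention to treat (ITT) and per protocol (PP) basis". Missing values in the ITT analysis are replaced by the last value carried forward, and participants who withdraw or do not comply are encouraged to keep providing data. Neither set is named as primary. Section 3.3 (Drug Accountability) sets compliance at 70% or more of the expected capsules.

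**The concern.** The power figure and the analysis do not use the same standard. A 95% interval excludes zero in the favourable direction only when the one-sided p-value is below 0.025, whereas the sample size allows 0.05. The protocol confines the one-sided choice to planning ("Using a one-sided independent samples t-test for the purpose of calculating sample size") and does not carry it into section 5.2. A result with a one-sided p-value between 0.025 and 0.05 would meet the sizing criterion while its 95% interval included zero, and the protocol would offer no way to settle the dispute.

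The inflation step has a second mismatch. Dividing 166 by 0.70 treats the whole 30%, non-compliers included, as absent from the analysis and the remainder as showing the full 3-point effect. An ITT analysis keeps the non-compliers and, through carried-forward values, many who withdraw. It therefore has more participants than 166, but possibly a smaller average effect. The stated 90% describes neither that analysis nor any other set that the protocol names as primary.

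The sponsor and ethics committees are thus given a 10% risk of missing a true 3-point VaDAS-cog effect. At the planned analysed number and on the two-sided standard, the risk is about 17%.

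**Working it through.** **Inputs.** Difference 3 on both scales, SD 6.56 (VaDAS-cog) and 5.31 (ADCS-ADL), level 0.05, power 90%, and loss of 30%, all from section 3.2. Allocation is 1:1 (section 3.3, blocks of 3 active and 3 placebo).

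**Formula.** For N analysed in total, n = N/2 per arm. The noncentrality is λ = difference / (SD × √(2/n)), with N − 2 degrees of freedom. Power is the probability that a noncentral t with parameter λ exceeds the critical value c. For a one-sided 5% test c is the 95th percentile of t; for a two-sided 5% test it is the 97.5th.

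**1. Reproducing the protocol's figures (one-sided).**
- VaDAS-cog, N = 166: λ = 3 / (6.56 × √(2/83)) = 2.946, c = 1.654, power 90.1%. The smallest N reaching 90% is 166, as stated.
- ADCS-ADL, N = 110: λ = 3 / (5.31 × √(2/55)) = 2.963, c = 1.659, power 90.3%. The smallest N is 110, as stated.
- Recruitment: 166 / 0.70 = 237.1, rounded up to 238, as stated.

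**2. The same N with a two-sided 5% test.**

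| Scale | N analysed | λ | c | Power |
|---|---|---|---|---|
| VaDAS-cog | 166 | 2.946 | 1.975 | 83.4% |
| ADCS-ADL | 166 | 3.640 | 1.975 | 95.1% |
| ADCS-ADL | 110 | 2.963 | 1.982 | 83.6% |

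For scale only: 90% two-sided power for VaDAS-cog would need 204 analysed.

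**3. ITT with all 238 analysed, VaDAS-cog, two-sided.** The protocol gives no dilution, so these are scenarios. If the affected 30% keep a share k of the benefit, the average effect is 3 × (0.70 + 0.30k).

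| Assumption for the 30% | Average effect | λ | Power |
|---|---|---|---|
| Full benefit (k = 1) | 3.00 | 3.528 | 94.0% |
| Half the benefit (k = 0.5) | 2.55 | 2.998 | 84.8% |
| No benefit (k = 0) | 2.10 | 2.469 | 69.1% |

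Break-even: analysing 238 at a diluted effect matches 166 at the full effect when the effect falls by about 1 − √(166/238) = 16.5%. Spread over 30% of participants, that is a loss of 0.165 / 0.30 = 55% of their benefit. ITT power is below 83.4% only if they lose more than that on average.

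**4. Both scales together.** This matters only if success on both is required, which the protocol does not say. With 166 analysed and two-sided tests, joint power at correlation 0 is 0.834 × 0.951 = 79.3%. At an assumed correlation of 0.7, a bivariate normal calculation gives 82.1%.

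**The case against.** The strongest reply is that nothing is concealed. Section 3.2 says twice that the calculation is one-sided, and 90% is the right answer to the question it poses. The hypothesis in section 1.2 is directional. Section 5.2 says how results are reported, not how success is decided, and a statistical analysis plan that is not shown here may fix the sidedness. The two-sided reading is therefore an inference from the 95% interval. That stands as a limit on the wording. It does not remove the mismatch: both statements are in the protocol, no passage plans a one-sided test or a 90% interval for the analysis, and section 5.2 tests for differences without a direction.

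A reader might go further and infer that true power is 83% at best. The documents do not support that. The 83% applies to 166 analysed; an ITT analysis restores up to 72 participants, and with no dilution its two-sided power is 94%, above the stated 90%. The 69% case assumes that the whole 30% gain nothing yet all contribute data. A participant can be classed as non-compliant after taking almost 70% of the capsules, and a carried-forward value may hold part of an effect, so partial benefit is plausible.

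A reader might also infer that ITT governs, or that both scales must succeed. The protocol names no primary analysis set and no success rule for the two scales, and 166 is compatible with a per-protocol set. Finally, the t-test stands in for the planned mixed model, which could shift every figure, and ADCS-ADL keeps about 95% at 166.

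**Conclusion.** The point holds in a limited form. The stated 90% for VaDAS-cog is a one-sided 5% figure. On the two-sided standard that matches the planned 95% intervals, 166 analysed give about 83% for VaDAS-cog and about 95% for ADCS-ADL. This rests on the protocol's own differences and standard deviations, on the t-test as planning method, and on reading the 95% interval as a two-sided 5% criterion.

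The inflation to 238 does not match an ITT analysis either, but the direction of that second error cannot be determined. Two-sided ITT power for VaDAS-cog lies between about 69% and 94%, depending on a dilution that the protocol does not state. It cannot be said that the design delivers less than 83%. The defect is a misdescribed power figure and an unspecified analysis set, not a demonstration that the trial is too small.

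**What to change.** In sections 3.2 and 5.2:

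- State that each primary test is two-sided at 0.05, matching the 95% confidence interval.
- Restate the power with 166 analysed as about 83% for VaDAS-cog and about 95% for ADCS-ADL, noting that these are t-test figures.
- Say which analysis set the power statement refers to.
- Split the 30% into withdrawal and non-compliance, and give the ITT power for VaDAS-cog as a range of about 69% to 94%, with the dilution assumed at each end.
- If success on both scales is required, say so and give the joint power as about 79% to 82%, for an assumed correlation of 0 to 0.7.

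Recruitment stays at 238 and conduct does not change. The cost is protocol wording and a stated power for VaDAS-cog that is less favourable than the present 90%.

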### Secondary efficacy endpoints

The secondary efficacy endpoints of the study will be the differences between the *SLT* and the placebo groups in the changes between baseline and 26-, and 52-week follow-up visits in:

- Scores of Clinician's Interview Based Impression of Change-plus (CIBIC-plus)
- Scores of additional executive function tests including CLOX and EXIT-25 from Baseline and 26-, and 52-week follow-up visits
- Scores of DEMQOL from Baseline and 26- and 52-week follow-up visits
- Scores of *Neuropsychiatric Inventory-Clinician rating scale* (NPI-C) from Baseline and 26- and 52-week follow-up visits
- Changes in MRI biomarkers from Baseline and the end of treatment assessment (52 week follow-up)

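### The MRI substudy's 52% power is correctly calculated, but for a test that averages the two scans in 50 complete pairs and not for the change endpoint

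*Protocol*

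**What the plan says.** Protocol section 3.2 (Sample Size) describes the MRI substudy as "comprising 50 samples with two matched groups measured at two time points". It names the test: "Between factor repeated measures analysis was used to compute the power". The inputs are given as "Assuming a medium effect size of 0.25" and a "between-measures correlation of 0.5 at 5% level of significance the power was found to be 52" per cent. The section adds that multiple testing may lower this further. Participants are invited to scanning until 50 have agreed. Under discontinuation, the same section says that withdrawn participants are not replaced.

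The preceding paragraph, on the main trial, does provide for loss: "Allowing for a total non-compliance/withdrawal rate of 30" per cent. The MRI paragraph has no such provision.

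Section 1.3 defines the endpoint. It opens "The secondary efficacy endpoints of the study will be the differences between the" two arms in their changes, and the MRI item reads "Changes in MRI biomarkers from Baseline and the end of treatment assessment (52 week follow-up"). Table 1 places the scans at week 0 and week 52. Section 5.1 describes volumetric, lesion and perfusion changes over 12 months.

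**The concern.** A between-factors repeated-measures test asks whether the two arms differ in the mean of their two scans. The first scan is taken before treatment, when randomised arms have no expected difference, so that mean is not what the endpoint measures. The endpoint asks whether the arms differ in how far they moved from baseline.

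The two questions respond in opposite ways to the scan-to-scan correlation. A high correlation makes change easier to detect and makes an average less informative. A power figure from the averaged test therefore misleads about the parameter that matters most in a two-scan design.

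The calculation also treats every enrolled participant as supplying a week-52 scan, although enrolment is capped and withdrawals are not replaced. What is at stake is how a null or positive MRI result will be read, since the protocol's only statement of the substudy's sensitivity belongs to another comparison.

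**Working it through.** **Inputs from section 3.2:** N = 50 in two groups, m = 2 scans, f = 0.25 (for two equal groups f = d/2, so d = 0.5 SD), correlation ρ = 0.5, α = 0.05. Power is from the noncentral F with 1 and N − 2 degrees of freedom (N − 3 for ANCOVA).

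**Step 1: reproduce the stated figure.** Between factors: λ = f²·N·m / (1 + (m − 1)ρ) = 0.0625 × 50 × 2 / 1.5 = 4.17. Power is 51.6%, which matches 52%. This identifies the test as the group main effect averaged over both scans, in 50 complete pairs.

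**Step 2: tests that address change.** Two readings of f = 0.25 are possible.

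- *A 0.5 SD difference at week 52 and none at baseline.* Change score: λ = d²·N / (8(1 − ρ)) = 0.25 × 50 / 4 = 3.125. Baseline-adjusted ANCOVA: λ = d²·N / (4(1 − ρ²)) = 0.25 × 50 / 3 = 4.17.
- *The same f entered in the group-by-time test.* λ = f²·N·m / (1 − ρ) = 0.0625 × 50 × 2 / 0.5 = 12.5. On the change scale this is a difference Δ with Δ² × 50 / (8 × 0.5) = 12.5, so Δ = 1.0 SD, twice the effect in the first reading.

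**Step 3: missing week-52 scans.** The protocol gives no MRI-specific rate, so losses of 10%, 20% and 30% (45, 40 and 35 pairs) are assumptions. Power at ρ = 0.5:

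| Test and effect | 50 pairs | 45 | 40 | 35 |
|---|---|---|---|---|
| Averaged test, protocol's formula | 52% | 47% | 43% | 38% |
| ANCOVA, 0.5 SD at week 52 only | 52% | 47% | 43% | 38% |
| Change score, 0.5 SD at week 52 only | 41% | 37% | 34% | 30% |
| Group-by-time, f = 0.25 | 93% | 91% | 87% | 82% |

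**Step 4: vary the correlation.** Values above 0.5 are assumptions. The averaged test uses the protocol's formula; the other two use 0.5 SD at week 52 only.

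| Pairs | Test | ρ = 0.5 | ρ = 0.7 | ρ = 0.9 |
|---|---|---|---|---|
| 50 | Averaged | 52% | 47% | 43% |
| 50 | Change score | 41% | 61% | 97% |
| 50 | ANCOVA | 52% | 68% | 98% |
| 35 | Averaged | 38% | 34% | 31% |
| 35 | Change score | 30% | 46% | 89% |
| 35 | ANCOVA | 38% | 52% | 91% |

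The first two rows of the step 3 table agree only because ρ = 0.5. The averaged test has error variance (1 + ρ)/2 and ANCOVA has 1 − ρ² = (1 − ρ)(1 + ρ). These are equal only when 1 − ρ = 1/2.

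**The case against.** The case for leaving the text alone has real force:

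- **The arithmetic is right.** The figure follows from its stated inputs and named test. A reader might infer a miscalculation, and there is none.
- **A sound analysis gives the same number.** ANCOVA with 50 pairs at ρ = 0.5 also yields 51.6%. This is true, but it is a coincidence of that one correlation, and at any other value the two part company.
- **The direction of the error is not fixed.** Depending on what f = 0.25 means, 52% is too high, about right or too low. This stands, and it rules out putting one corrected number in its place.
- **The 30% is not a scan-loss rate.** It combines non-compliance and withdrawal in the main trial. Section 5.2 encourages people who stop treatment to continue with data collection, and section 3.2 asks withdrawals to attend the end-of-treatment visit. This stands too: 35 pairs is a scenario. It does not justify assuming no loss at all.
- **Low power is already admitted.** The protocol reports only 52% and warns that multiplicity will lower it. That warning does not touch the choice of test, the effect scale or missing scans.

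A reader might also infer that the averaged test will be used for the analysis and would hide a treatment effect. With a difference at week 52 only, it would indeed have just 17% power with 50 pairs and 13% with 35. But the protocol does not plan that analysis. Section 5.1 describes change between two time points, and section 5.2 specifies mixed models for group differences over time. The word matched, for groups formed by randomisation, is loose wording with no shown effect on the result.

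**Conclusion.** The point holds as a mismatch between the power calculation and the endpoint, with no allowance for missing second scans. It is not an arithmetic error, and the documents do not support stating that the true power is 38% or any other single value. At the protocol's own correlation, plausible power runs from 30% (change score, 35 pairs, 0.5 SD at week 52 only) to 93% (group-by-time, f = 0.25, 50 pairs). The spread comes from three things the text leaves open: what effect 0.25 measures, how many week-52 scans will be obtained, and whether 0.5 is a realistic scan-to-scan correlation. If that correlation were 0.9, ANCOVA with 35 pairs would have about 91%. The consequence is moderate: a secondary endpoint in a substudy, with no effect on the main trial's sample size.

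**What to change.** In section 3.2, replace the MRI calculation with one for the between-group difference in change, or for the week-52 value adjusted for baseline. State what f = 0.25 stands for on that scale, preferably as a difference in SD units. Allow explicitly for missing week-52 scans, saying whether the main trial's 30% is assumed to apply or a smaller loss is. Report power as a range over scan loss and over the scan-to-scan correlation, as in the tables above. The cost is a recalculation and a few sentences of protocol text. No extra scans are needed; only the stated figure changes.
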